## Background

Mechanical ventilation (MV) support is crucial for patients with acute respiratory distress syndrome (ARDS). While there is agreement on the preference for lower tidal volumes [1, 2], there is relatively little consensus on the selection of positive end-expiratory pressure (PEEP) [3–9]. Traditionally, lower PEEP has been used [10, 11], but low PEEP can lead to increases in oxygen desaturation and hypoxaemia [4, 12] and worsening of lung injury, indicated by greater use of rescue therapies and deaths after rescue therapy [9]. High PEEP can increase alveolar recruitment, but can decrease cardiac output and lead to further lung injury due to barotrauma and/or volutrauma [13] or overdistension [4, 9].

PEEP can be optimised to reduce hypoxaemia [6] and intrapulmonary shunting [7] and improve gas exchange [8] and oxygenation [4, 14, 15], by maintaining recruitment of injured or collapsed alveoli [13]. In patients with ARDS, PEEP reduces ventilator-induced lung injury (VILI) [4, 9], increases recruitment [14–16], and reduces inflammatory mediators in plasma and bronchoalveolar lavage fluid [8]. MV strategies combining low tidal volumes with recruitment manoeuvres (RMs) and higher PEEP to prevent VILI have been hypothesized as ideal for lung protection [6, 17]. However, currently, there is still no standardized approach to the selection of this optimal PEEP, or to deciding how often PEEP should be adjusted or recalculated.

Reports from experimental animal trials performed by Carvalho et al., Suarez-Sipmann et al. and Lambermont et al. [18–20] indicate that pigs induced with ARDS experience minimal respiratory elastance at a specific PEEP associated with higher oxygenation, maximum recruitment, and higher functional residual capacity, all without signs of lung overdistension. Equally, it has been proposed that PEEP should be set whereby the lung has minimal respiratory elastance (or maximum compliance), which could be clinically beneficial by balancing the risks of PEEP that is set too low or too high [21–23]. Aside from the work by Suter et al. [21], Pintado et al. also showed that PEEP selection at minimal elastance is beneficial to patients [22]. Despite some consistent findings, the application of minimal elastance PEEP selection remains limited and hindered by the lack of an objective, reliable, and easy-to-use method to determine elastance at the bedside in real time.

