## Methods and trial design

### Study design and setting

The CURE RCT is a two-arm RCT comparing model-based mechanical ventilation (MBV) with current standard practice mechanical ventilation (SPV) in patients with a ratio of partial pressure of arterial blood oxygen (PaO2)/fraction of inspired oxygen (FiO2) (P/F ratio) ≤ 200. It is to be conducted in a single-centre hospital intensive care unit (ICU) at Christchurch Hospital in Christchurch, New Zealand.

The primary objective is to assess the impact of model-based ventilation in PEEP selection (MBV) therapy on clinically significant patient outcomes and patient-centred quality of care metrics. The other objectives of this study include (1) to provide the knowledge and methods to make care more patient-specific and timely to optimise treatment and improve outcomes in a large cohort of critically ill patients and (2) to improve the understanding of the pathophysiological basis of critical illness through what we learn about the hourly and daily evolution of lung injury in terms of patient-specific elastance and response to care through this study.

The primary outcome of this study is the area under the curve (AUC) of PaO2/FiO2 over the period of mechanical ventilation. Secondary outcomes include length of time of MV (LoMV), ventilator-free days (VFD) up to 28 days, ICU and hospital length of stay (LoS), AUC of SpO_2_ (oxygen saturation)/FiO_2_ during MV, number of desaturation events (frequency and fraction of time SpO_2_ < 88%), changes in respiratory mechanics and chest x-ray index scores, rescue therapies (prone positioning, nitric oxide use, extracorporeal membrane oxygenation (ECMO)) and hospital and 90-day mortality. These outcomes and their corresponding four levels of specification based on Zarin et al., 2011 is shown in Table 1. The secondary analysis includes comparison of the means of LoMV, VFD, hospital and ICU LoS, 90-day mortality, chest x-ray index scores and rescue therapies used.

**Table 1 Tab1:** Four levels of specification in primary and secondary outcomes

Level 1 Domain	Oxygenation		MV		Length of stay			Other	
Level 2 Specific domain	AUC P/F ratio	AUC Spo2/FiO2	Length of MV	Ventilator free days (VFD) up to 28 days	Hospital	ICU	90-Day mortality	Chest x-ray index scores	Rescue therapies
Level 3 Specific metric	Difference in AUC		Number of days	28 days – days of MV	Number of days		Time to event	Index scores over period of MV	Number of therapies used

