#### Exclusion criteria

The exclusion criteria are:
P/F ratio > 300 on any level of PEEP or FiO_2_P/F ratio > 200 on FiO_2_ = 50% and PEEP = 5Ventilated > 48 h (including time spent in another hospital)Not expected to be ventilated for another 48 hAge < 16 yearsAny medical condition associated with a clinical suspicion of raised intracranial pressure and/or measured intracranial pressure ≥ 20 mmHgHigh spinal cord injury with loss of motor function and/or significant weakness due to neurological diseaseBarotrauma (pneumothorax, pneumomediastinum, subcutaneous emphysema or any intercostal catheter for the treatment of air leak)Asthma as the primary presenting condition or history of significant chronic obstructive pulmonary diseaseMoribund and/or not expected to survive for > 72 hAgreed limitations of care due to co-morbidities, or not expected to survive 90 daysLack of clinical equipoise as determined by ICU medical staff managing the patient (for example, if the patient has unremarkable findings on chest x-ray, with the possibility of thrombotic or fat pulmonary emboli)Previous enrolment in the CURE RCT

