#### Other patient information

The following information will be collected:
Demographic data
Age, weight, heightEthnicityAcute Physiology and Chronic Health Evaluation (APACHE) II and IIIJ, Simplified Acute Physiology Score (SAPS) II, Australian and New Zealand Risk of Death (ANZROD) from the ANZICS CORE databaseWaveform data from physiological monitors including:
SpO_2_ - used to detect desaturation eventsBlood pressureHeart rateEnd-tidal CO_2_Arterial blood gases:
Measured at least twice dailyBefore and after any RM_Max_ or PUMPRoutine biochemical analysis (up to daily)
Electrolytes, urea, creatinine, glucose, liver testsFull blood countPatient’s findings on radiology (chest x-ray and computed tomography (CT))Patient position during MV (to account for data variation resulting from changes in patient position)Rescue therapies: (i) prone positioning, (ii) nitric oxide (iii) ECMOLength of time of mechanical ventilation (LoMV) or ventilation-free daysAmount of sedation - to account for possible data variation resulting from use of different sedativesDuration of ICU stayFrequency and duration of renal support therapiesAll causes of ICU, hospital and 90-day mortality

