### Adverse event (AE) and SAE reporting

(AEs are defined as any unexpected change in physiology in a study participant associated with either the RM_max_ or PUMP. This does not necessarily have to have a causal relationship with the aforementioned procedures. Typically, this would be an unexpected, non-life-threatening event, which rapidly resolves following simple corrective measures. For example, hypotension will occur in most participants undergoing an RMmax or PUMP. However, if the procedure had to be shortened or abandoned, but the participant recovered with simple corrective measures (e.g. temporarily increasing noradrenaline by ≥ 5 mcg/min) or giving > 500 ml fluid bolus) this would be recorded as an AE. It is very important these events are accurately recorded as risk factors for AEs that need to be defined when carrying out RMs (as seen in Additional file 3).

SAEs are defined as any untoward medical occurrence that (1) results in death; (2) is life-threatening; (3) prolongs hospitalisation or (4) results in disability or incapability. However, baseline mortality in the patients in intensive care who are enrolled in the trial will likely be high due to the critical illness necessitating admission to the ICU. Despite attempts at prevention, trial participants will frequently develop life-threatening organ failure(s) unrelated to study interventions. Events that are a part of the natural history of the primary disease process or expected complications of critical illness will not be reported as SAEs in this trial. Additionally, events already defined and reported as study outcomes, such as mortality or re-admission to the ICU, will not be labelled and reported separately as SAEs unless they are considered to be causally related to the study intervention or are otherwise of concern in the investigator’s judgement.

SAEs will be reported to the principal investigator within 24 h of any investigator becoming aware of the event. The minimum information to report includes:
Patient trial identifierThe nature of the eventThe time the event commenced and ceasedAn investigator’s opinion of the relationship between study involvement and the event (not related, unlikely, possibly, probably or definitely related)Whether treatment was required for the event and what treatment was administered

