SAEs could include pneumothorax, hypotension leading to cardiac arrest, transient desaturation leading to severe or prolonged desaturation, tachycardia, bradycardia, arrhythmia, anaphylaxis and unintended protocol deviations.

In the unlikely event of a physical injury to the participant as a result of their participation in this study, they will be eligible to apply for compensation from the Accident Compensation Corporation (ACC) NZ within its limitations. If the participant’s family/friend have any questions about the ACC, they will be able to ask the researchers for more information before they agree to take part in this trial.

ACC cover is not automatic and their case will need to be assessed by the ACC according to the provisions of the 2001 Injury Prevention Rehabilitation and Compensation Act. If the claim is accepted by the ACC, the patient still might not receive compensation. This depends on a number of factors such as whether they are earners or non-earners. The ACC usually provides only partial reimbursement of costs and expenses and there may be no lump sum compensation payable. There is no cover for mental injury unless it is a result of physical injury. If your relative or friend has ACC cover, generally this will affect their right to sue the investigators.

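### The rules for recording barotrauma differ by arm and no outcome list contains it, so safety counts built from the AE and SAE reports could differ between arms with no true difference

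*Protocol article*

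**What the plan says.** The Background of the protocol article states that high PEEP "can decrease cardiac output and lead to further lung injury due to barotrauma and/or volutrauma". Barotrauma at entry is an exclusion, defined under Exclusion criteria as "pneumothorax, pneumomediastinum, subcutaneous emphysema or any intercostal catheter for the treatment of air leak", so any later case is new.

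The secondary outcomes in Study design and setting run from "Secondary outcomes include length of time of MV (LoMV), ventilator-free days (VFD) up to 28 days, ICU and hospital length of stay (LoS") through oxygenation measures to "changes in respiratory mechanics and chest x-ray index scores, rescue therapies (prone positioning, nitric oxide use, extracorporeal membrane oxygenation (ECMO)) and hospital and 90-day mortality". Barotrauma is not among them, nor is it in the abstract, Table 1 or the Study outcome section. The chest x-ray outcome is an index score, not a count of air leaks. The Stopping rule concerns mortality only.

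Three sections govern how barotrauma is recorded:

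- **RM checklist.** Before any recruitment manoeuvre, staff check for barotrauma since enrolment. If it is new, the participant is withdrawn but still followed up, and an SAE report is required.
- **Adverse event (AE) and SAE reporting, definitions.** AEs are tied to RM_Max or PUMP. For SAEs, "expected complications of critical illness will not be reported as SAEs in this trial".
- **The same section, examples.** "SAEs could include pneumothorax, hypotension leading to cardiac arrest, transient desaturation leading to severe or prolonged desaturation".

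Separately, Other patient information lists each patient's "findings on radiology (chest x-ray and computed tomography (CT") among the data to be collected, without restriction to one arm.

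**The concern.** The trial is open label (Randomisation and blinding), and PEEP selection is what it tests. A harm linked to PEEP should be counted in the same way in both arms. As written, the occasions on which staff must look for barotrauma and report it follow the recruitment manoeuvre schedule, and that schedule is itself part of the treatment difference. A pneumothorax in an MBV patient will usually meet a firm rule at the next scheduled PUMP. The same event in an SPV patient for whom no manoeuvre is planned depends on whether staff who know the arm regard it as an SAE or as an expected complication of critical illness.

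The Data Monitoring Committee section says the committee reviews the SAE reports it receives, and Study outcome says the trial may lead to MBV being rejected as a standard of care. A barotrauma count that depends on the reporting route could show an excess in MBV that does not exist, or mask a true reduction.

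**Working it through.** **Step 1. Set the recording routes side by side.**

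| Route | MBV | SPV |
|---|---|---|
| Mandatory SAE report (RM checklist) | At RM_Max and before each PUMP. PUMP is twice daily for up to 10 days: 2 × 10 = up to 20 scheduled checks, plus RM_Max | Only before a staircase manoeuvre, which is left to clinical judgement; can be 0 |
| AE definition (AE and SAE reporting) | Applies: tied to RM_Max and PUMP | No route: Recruitment manoeuvres (RM) restricts both procedures to MBV |
| SAE outside the checklist (AE and SAE reporting) | Judgement, arm known | Judgement, arm known |
| Radiology findings (Other patient information) | Collected | Collected |

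The figure of 20 is a maximum, because PUMP stops earlier when the conditions under Procedures for the intervention group are met. The first two routes differ by arm. The third is worded the same for both but is discretionary. The fourth is common to both, but no stated outcome turns it into a barotrauma count.

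The sections also disagree with one another. The RM checklist makes new barotrauma a reportable SAE without qualification, whereas the SAE section gives pneumothorax only as a possible example and exempts expected complications.

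**Step 2. Effect of unequal capture.** The documents give no barotrauma rate and no capture rate, so there is no planned figure to reproduce; the values below are assumptions. Let p be the true rate in both arms, with capture c_M in MBV and c_S in SPV.

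- Reported risk ratio = c_M / c_S
- False risk difference = p × (c_M − c_S)

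With c_M = 1:

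| c_S | Risk ratio | False difference, p = 5% | p = 8% | p = 10% |
|---|---|---|---|---|
| 0.8 | 1/0.8 = 1.25 | 1.0 point | 1.6 | 2.0 |
| 0.6 | 1/0.6 = 1.67 | 2.0 | 3.2 | 4.0 |
| 0.5 | 1/0.5 = 2.0 | 2.5 | 4.0 | 5.0 |

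At p = 5% and 160 per arm, the true count is 0.05 × 160 = 8 events in each arm. The reports would show 8 in MBV against 6.4, 4.8 or 4 in SPV. In this pattern the error runs against MBV.

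**Step 3. Precision of a common count.** The 160 per arm is taken from Sample size study. Half-width of the 95% interval = 1.96 × √(2p(1 − p)/160). At p = 5% this is 1.96 × √(2 × 0.05 × 0.95/160) = 0.048, or 4.8 points. Detectable rates are at two-sided 5% and 80% power.

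| Assumed SPV rate | Half-width (points) | Detectable MBV rate | Power for a doubling |
|---|---|---|---|
| 3% | 3.7 | 11.0% | 25% |
| 5% | 4.8 | 14.2% | 40% |
| 8% | 5.9 | 18.6% | 60% |
| 10% | 6.6 | 21.4% | 71% |

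**Step 4. Compare the two.** At 5%, halved SPV capture shifts the difference by 2.5 points against a half-width of 4.8 (2.5/4.8 = 0.52). At 10% the ratio is 5.0/6.6 = 0.76. The shift is smaller than the sampling error, so on its own it would not usually produce a significant result. It would still move the estimate by a large share of its margin of error, and a larger sample would not remove it.

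**The case against.** The best defence is that the article already provides for barotrauma. The checklist report is compulsory and applies in either arm, since Standard practice SRM sends control patients through the same checklist. Pneumothorax heads the list of example SAEs with no limit to one arm, and the SAE definition itself is arm-neutral. Recruitment manoeuvres (RM) says the recorded data will be used to assess the safety of all three manoeuvres, including the control arm's. Additional file 3 on AE recording, the full protocol and any SAP are not shown, and a safety table may be in one of them.

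Much of this stands, and it rules out several stronger readings that a reader might infer:

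- **That barotrauma reaches the analysis only through discretionary reports.** It does not: the checklist report is mandatory.
- **That the trial cannot give an unbiased comparison.** The documents do not support this, because radiology findings are collected in both arms and could supply a common count.
- **That only MBV patients are exposed to high airway pressure.** A staircase manoeuvre takes an SPV patient to the same 40–43 cmH2O, and MBV selects PEEP at minimal elastance rather than high PEEP. The contrast is scheduled against discretionary manoeuvres and checks.
- **That bias has been shown.** It has not; the capture rates above are illustrations.

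The defence does not answer the asymmetry in the stated rules. An SAP can add a table, but it cannot recover control events that were never reported unless a common source is specified.

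**Conclusion.** The point holds as one of unequal recording. Followed as written, the AE and SAE rules oblige staff to look for and report barotrauma on a schedule in MBV and only incidentally in SPV, and they leave the remaining cases to unblinded judgement. With no barotrauma outcome named, nothing stated in the article corrects for this.

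The size is unknown. Under assumed equal true rates of 5% to 10% and full MBV capture, SPV capture of 50% to 80% gives false risk ratios of 2.0 down to 1.25 and false differences of 1.0 to 5.0 points. The direction depends on MBV being captured more completely, which is what the checklist schedule suggests; judgement outside the checklist could act either way. This should be corrected but does not threaten the primary analysis.

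**What to change.** 1. Reconcile the RM checklist with the AE and SAE section so that reporting of new barotrauma depends neither on arm nor on a manoeuvre being planned. The SAE section also exempts events already reported as study outcomes unless they are thought causally related or are otherwise of concern to the investigator. The revised text should say how that exemption applies once barotrauma is a named outcome.
2. Name new barotrauma, by the definition already in Exclusion criteria, as a secondary safety outcome. Count it from randomisation to day 28 in every randomised patient, including those withdrawn under the RM checklist, whatever the SAE label. The sources are the radiology findings already collected plus chest-drain insertion abstracted from the clinical record. Drain records are not in the current data list and would have to be added.
3. Report the risk difference with a 95% confidence interval by randomised arm, and show it in the closed interim reports to the DMC.
4. Report the number of chest images per arm alongside. The article states no imaging schedule, so imaging is presumably clinically triggered and some detection imbalance may remain.

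The cost is a little extra abstraction by the research nurses and one table, with no new imaging. The comparison will be imprecise (Step 3), so it should be presented as an estimate rather than a test. Trial status says recruitment had not begun, so the change could be made before the first patient.

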### Data Monitoring Committee (DMC)

An independent DMC comprising experts in clinical trials, biostatistics and intensive care medicine is established before patient enrolment, to review all trial protocols and oversee and advise on this trial. The DMC will be forwarded a copy of all SAE reports as soon as they become available to the trial investigators. The DMC will review all SAE reports that they receive and report back to investigators if any further action is required.

### CURE RCT composition

The steering committee of the CURE RCT comprises the primary investigators [name], [name], [name] and [name]. The clinical data are collected by research nurses in the ICU and mechanical ventilation data and oxygenation (bedside monitor) data will be collected by researchers from the UC. All study data will be stored in the double-encrypted repository at UC. Data will be interpreted by participating researchers. The open and closed case interim reports will be compiled by [name] every 6 months and when 50 and 100 patients have been included. The DMC will have authority to continue or stop of the trial based on the interim reports.

## Discussion

Mechanical ventilation using PEEP set at minimum elastance has long been investigated in both experimental and clinical trials. These studies ranged from healthy patients under general anaesthesia to those with ARDS. However, only a few studies have investigated the clinical potential of PEEP set at minimum elastance. Recent studies by Pintado et al. [22] and [name] et al. [23] have shown the potential and feasibility of ventilating patients using minimum elastance PEEP. However, setting PEEP based on elastance is problematic due to the increased need of muscle relaxants, protocol burden and potential contradictory findings [22, 23]. The pilot trial was also underpowered and thus, a larger clinical trial such as the CURE RCT is required to provide further insight and validate the potential benefit of optimising mechanical ventilation PEEP with model-based methods.

The CURE RCT implements a protocolised staircase PEEP recruitment manoeuvre together with novel computer software to calculate respiratory system elastance in real time. The computer software, CURE Soft [25], uses a single compartment lung model [39] together with other model-based approach [24, 40] to aid clinicians during PEEP selection. This process potentially reduces selected PEEP variability and provides more consistent clinical guidance.

There are several limitations of the CURE RCT design that should be noted. In particular, the RM is a double-staircase manoeuvre and is design specific. Studies have shown that not all patients benefit from RMs [41, 42], and the benefit of an RM is dependent on the patient-specific disease state, as well as the design of the RM. The double-staircase RM in this trial was designed to assess lung recruitment and provide consistent PEEP titration. It is noted that not all patients included in this study will necessarily demonstrate alveolar lung recruitment.

Another limitation worth noting is the control group clinical protocol. Clinically, there is relatively little consensus an optimal mechanical ventilation mode. Thus, the standard practice ventilation in the participating hospital relies on general approaches [2] and is highly variable between clinicians. There may be no equal comparator for a mechanical ventilation study resulting from this variability. Patients recruited to the CURE RCT will have the MV mode set to bi-level ventilation in both the intervention and the control group; it is debatable that bi-level ventilation may lack certain ventilation advantages. However, this procedure will reduce variability and provides the opportunity for fair comparison between groups.

In the participating ICU, there are > 700 patients per year requiring invasive MV; however, only an average of < 5 patients were diagnosed with ARDS as the primary diagnosis per year. ARDS is nearly always regarded as a complication of an acute process. One concern is that the desired sample size cannot be achieved. However, this number is also too small compared to reports [43, 44]. The small number may be due to changes in the ARDS definition [27, 45] and misdiagnosis [46]. Estenssoro et al. [46] report that misdiagnosis could occur due to delayed screening. Thus, in the CURE RCT, any patient requiring invasive mechanical ventilation is screened immediately, as per Villar et al. [27], whereby the P/F ratio is measured at PEEP = 5 cmH_2_O, and FiO_2_ = 50%. Equally, retrospective screening was also performed and identified > 200 patients eligible for the trial per year. Hence, a 3-year study is planned to achieve the target sample size at an estimated recruitment rate of 50%.

